## Abstract

(1) *Background:* Current international policy for schistosomiasis and soil-transmitted helminthiasis (STH) control emphasises mass administration of deworming drugs in school-based programmes. However, this approach is insufficient to control the transmission of these diseases, and their burden in non-school cohorts is recognised, albeit under-researched. This research will investigate the feasibility and acceptability of expanding access to praziquantel (PZQ) against schistosomiasis, and albendazole (ALB) against STH, to communities in selected transmission settings in Ghana. (2) *Methods:* A three-site longitudinal study will be implemented to investigate the effectiveness of expanding treatment strategies for PZQ and ALB to community members. In the context of community mass drug administration (to preschool children, school non-attending children, and adults, including pregnant women), the intervention will be assessed in a random sample of community members, at baseline with follow-up at 6, 12, and 18 months. In each community, 658 participants will be enrolled, and 314 followed up at each time point. The primary outcome measure is the prevalence of infection of *Schistosoma haematobium* and/or *S. mansoni* at study endpoint, as assessed by longitudinal surveys. Secondary outcomes are to quantify the infection of schistosomiasis and STH infections in non-treated cohorts, reductions in prevalence of STH, and intensity of schistosomiasis and STH, and treatment coverage. Nested within this study will be qualitative, cost-benefit, and cost-effectiveness evaluations that will explore accessibility, feasibility, and economic impact of expanded treatment from different complementary perspectives. (3) *Discussion:* Using a multidisciplinary approach, this study will generate evidence for improved availability, acceptability, affordability, and accessibility to deworming drugs against schistosomiasis and STH to individuals and communities in Ghana. This is likely to have considerable research, programmatic, and political value to contribute evidence for national programme policy development within Ghana, and, more broadly, World Health Organization policy development.

## 1. Background

Schistosomiasis (*Schistosoma mansoni* and *S. haematobium*) and soil-transmitted helminthiasis (STH; *Ascaris lumbricoides*, *Trichuris trichiura*, *Necator americanus*, *Ancylostoma duodenale*, and the less-researched *Strongyloides stercoralis*) infections constitute a major public health problem and share the majority burden of disease from the group of neglected tropical diseases (NTDs) [1]. Globally, schistosomiasis and STH cause an estimated disease burden exceeding eight million disability-adjusted life years [2]. Infections contribute heavily to intestinal damage, anaemia, impaired physical, and mental growth in children, and, for schistosomiasis, urinary and genital organ damage with important differences in males and females [3,4]. In schistosomiasis-endemic areas, symptoms of both female genital schistosomiasis (FGS) and male genital schistosomiasis (MGS) can manifest after many years of infection, commencing from preschool-aged exposure [5]. Unfortunately, assessment of pathological changes and symptoms in all of the cohorts is under-researched and these disorders are under-diagnosed in the developing world [6]. FGS leads to stigma and social isolation, with symptoms including menstrual irregularity, menorrhagia (heavy bleeding), pain during or after sexual intercourse (dyspareunia), post-coital bleeding, ectopic pregnancy, miscarriage, and sub-fertility [7,8]. Schistosomiasis and STH are endemic in many countries, including Ghana, with STH being prevalent in most regions, and schistosomiasis proximal to water bodies containing *Bulinus* or *Biomphalaria* snail intermediate hosts [9]. People contract schistosomiasis from contact with water containing *Schistosoma* cercariae. STH life cycles involve environmental contamination with faeces containing helminth eggs; therefore, major risk factors include poor hygiene, sanitation, and access to clean water [10,11].

Mass drug administration (MDA) programs using praziquantel (PZQ) against schistosomiasis, and benzimidazole drugs (albendazole (ALB) or mebendazole (MBD), according to country) against STH, primarily focus on periodic treatment of school-aged children in school-based programmes (with some provision of STH treatments to preschool-aged children in some areas) [12]. Historically, this has been based on the assumptions that most attributable morbidity would be reduced by treating the school-aged cohort; that potential anthelmintic resistance is held in check by focusing on the school-aged cohort; and, that utilisation of existing school infrastructure is the most feasible and cost-effective means of delivering preventive chemotherapy programmes in resource-constrained settings [13,14]. However, morbidity in non-school cohorts does occur, meaning that deworming school-aged children alone is an imperfect strategy, particularly after years of MDA programmes [5,13]. With the current strategy, the burden of disease in preschool-aged and adult cohorts is therefore inadequately researched, and subsequently, under-prioritised in health programmatic planning. Inequity of access to deworming drugs by children who are not in school (for a variety of reasons, including the interplay of poverty and gender norms), and adult cohorts is a recognised problem [15,16,17,18,19,20]. Data demonstrating prevalence in vulnerable groups, treatment benefits to these groups, and feasibility of expanding access, are required to effect policy change. Despite considerable progress, at present WHO 2020 targets of treating 75% of school-aged children annually for morbidity control [21] are not yet being achieved [22], and, consequentially, millions of individuals suffer long-term debility, which could and should be avoided. In 2015, reported deworming coverage of school-aged children was 42.2% for schistosomiasis, 63.3% for STH; and, coverage of preschool-aged children for STH was 48.2% [23].

Assessing the effectiveness of increasing MDA access to broader community groups is a considerable global research priority. Thus far, research has focused on mathematical modelling studies [24,25,26,27] for STH, which indicate benefits of expanded treatment strategies. Impetus to provide an epidemiological evidence base is growing. A large-scale randomised controlled trial (RCT) investigating alternative treatment strategies for STH is under way, with anticipated results by 2018 [28]. An additional multi-site series of cluster RCTs will commence in 2017, to determine the feasibility of interrupting STH transmission and develop an implementation plan for scale-up in Malawi, Benin, and India [29]. Both of the initiatives focus on treatment strategies for STH. For schistosomiasis, the Schistosomiasis Consortium for Operational Research and Evaluation (SCORE) is undertaking studies in Kenya, Mozambique, Tanzania, Cote d’Ivoire, and Nigeria to investigate gaining and sustaining control in moderate-heavy transmission settings [30]; whilst extremely beneficial, these studies are assessing outcomes in school-aged children and do not longitudinally follow up the same individuals. Also associated with SCORE, studies in Zanzibar [31,32] have focussed on expanded treatment strategies to understand the thresholds and combined activities that are needed for elimination. This agenda-defining work is, however, focussed in a country that has experienced three decades of dedicated schistosomiasis control activities. Therefore, multidisciplinary work in other endemic countries is needed. Widespread elimination of schistosomiasis will almost certainly need the integrated use of preventive chemotherapy, snail control, behavioural modification, water, sanitation and hygiene (WASH) improvements, and perhaps eventually a prophylactic or transmission-blocking vaccine [9]. A recent meeting, ‘NTDs: Women and girls in focus’, discussed the importance of better understanding ways to ensure MDA programmes reach and reflect the needs of all groups by gender and age [33]. 

In Ghana, annual MDA is well-established and political motivation high, making it an excellent site in which to research concentrated treatment strategies. Implementation research will explore the feasibility and acceptability of expanding treatment to preschool-age children, out-of-school (school-aged) children, and adults, including pregnant women in selected community sites. The aim is to demonstrate that PZQ and ALB treatments are needed and can be up-scaled and delivered to these demographical groups (which, particularly for PZQ, are not presently targeted within national control programmes), achieving adequate treatment coverage, and resulting in more rapid declines in infection and disease state than annual school-based treatment. Research components include epidemiological, parasitological, social science, and health economics analyses, conducted across an international, multi-stakeholder environment. This study is anticipated to reduce prevalence and intensity of infection of schistosomiasis and STH, increase treatment coverage, and provide evidence to ensure more equitable access to vulnerable groups. In turn, this will help to strengthen the broader health system and generate evidence for improved availability, acceptability, affordability, and accessibility of these NTD interventions to individuals and communities. 

## 2. Design/Methods

A multi-site longitudinal study will be conducted in Ghana to investigate the effectiveness of expanding treatment strategies for PZQ and ALB to community members in a peri-urban setting, where the risk of schistosomiasis and STH is considerable. The intervention will be assessed at 6, 12, and 18 months. Nested within this study will be qualitative and socio-economic evaluations that will explore the accessibility, feasibility, and economic impact of expanded treatment from different complementary perspectives. 

The specific objectives are:To conduct targeted baseline parasitological and epidemiological surveys to describe infection levels of schistosomiasis and STH, and associated WASH and morbidity indicators;To assess expanded annual community treatment in reducing prevalence of schistosomiasis and STH;To assess community understanding of the current MDA programme and its strengths and weaknesses and economic aspects of whole community treatment;To assess the acceptability and feasibility of introducing an alternative treatment strategy to the current treatment regimen from different perspectives;To investigate different levels of access and factors influencing scale-up of PZQ and ALB treatment in areas with limited treatment coverage.

## 3. Study Area and Site Selection

Due to the highly spatially focal nature of schistosomiasis, regions have been purposively selected according to known endemicity (based on National NTD Control Programme data). Communities within these regions have been selected based on prevalence of at least 10% of schistosomiasis infection (being *S. mansoni* or *S. haematobium*, or both), and proximity to water bodies containing intermediate snail hosts that has previously been ascertained ([name] unpublished). Typically, STH are co-endemic with schistosomiasis in these regions, but are not the basis for site selection, which is the focused on a peri-urban setting surrounding a manmade reservoir. In Ghana, most health care is provided by the government and is largely administered by the Ministry of Health and Ghana Health Service (GHS). There are five levels of health care provision: health posts, health centres and clinics, district hospitals, regional hospitals, and tertiary hospitals. Administratively, GHS is organized at national, regional, and district levels [33]. There are 110 health districts. For Ghana, three communities were selected in Ga South District (Greater Accra Region) (Figure 1). Due to the highly focal nature of disease, we will use routine data collected by GHS and CSIR to serve as controls.

## 4. Study Design

This longitudinal study will comprise baseline and follow-up surveying of the same individuals. Baseline surveying will involve screening urine and stool samples from a random selection of participants to assess infection prevalence and intensity, and conducting questionnaires to determine associations with WASH and morbidity from both schistosomiasis and STH. Qualitative focus group discussions and in-depth interviews will be held with community members and key informants to assess the understanding of the current MDA strategy, its strengths, and weaknesses, and to identify the feasibility and acceptability of expanding treatment in communities. Comparisons will be made: (i) after 6, 12, and 18 months; and, (ii) to the provision of annual MDA in the regular National School-Based Deworming Programme in schools in the same health districts, at the same time points as a means of comparison to the existing school-based deworming programme in similar prevalence settings. Drug treatment coverage for each survey will also be measured.

This study will involve expanding access to PZQ+ALB treatment for the broader population, including preschool-aged children, out-of-school school-aged children, and adults, including pregnant women. An annual community-based PZQ+ALB treatment will be provided by community health nurses and trained field staff, with cross-checking of enrolled school-aged children so as not to double-up treatments that have been provided in school-based MDA. Treatment will be provided at baseline and 12 months, and the associated reductions in prevalence and intensity of schistosomiasis and STH will be assessed (Figure 2). Parasitological examinations and questionnaires will be conducted on a random sample of participants to determine associations with morbidity from both schistosomiasis and STH, and investigate the feasibility of scale-up. An experienced and trained social science team will conduct qualitative interviews with teachers that are involved in administering annual MDA, and focus group discussions with purposively selected groups of participants by gender, age, and socio-economic status, as well as parents and caregivers.

For comparison purposes, three school-based sites in the same health districts as the study sites will be selected. In these schools, a random sample of school-aged children who currently receive annual MDA will be selected to participate in parasitological examinations and questionnaires, to enable comparison to the national school-based deworming programme. These data and treatment coverage data, available from the national NTD Control Programme, will be analysed for schools in the same health districts that are not included in the surveys. Due to ethical concerns about conducting parasitological testing for schistosomiasis in communities without the provision of treatment, and where there is no existing opportunity for treatment referral, community sites will not be used for comparison purposes in these studies. This is supported by school sites being the existing MDA unit.

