## 6. Individual Random Selection for Parasitological Examinations and Questionnaires

The study is an augmentation to the current standard of care (annual school-based MDA). With a longitudinal study design, random selection is only required at the individual level for parasitological and epidemiological investigations; all of the individuals in the community will be offered treatment. In each community, following sensitisation, households will be enumerated, with approximate number of residents recorded. Based on the number of households and indicative number of residents in each community, households will then be randomly selected according to a process of selecting every other (odd number houses) household to achieve the sample size. Where a household, or an individual within a household refuses, or is absent during the study, the household will be replaced by the next enumerated household. All the residents within the selected households will be requested to provide urine and stool specimens, and to complete questionnaires. At this stage, individual consent will be elicited, with age, sex, and school-attending status recorded and a unique participant identification number allocated. Selection will proceed until the minimum sample size is achieved. All community members will be invited to receive treatment, with additional consent elicitation by field staff. Treatments will be directly observed, and treatment coverage data will be recorded for all individuals.

For comparison to annual school-based MDA, a junior school (comprising children aged 6–14 years in classes 1 to junior high 3) will be selected at the time the national NTD Control Programme visit occurs. Prior to the deworming, school directors and class teachers will be asked to prepare class lists with the name, age, and sex of the children. Class lists will be imported into Microsoft Excel and each individual will be assigned a computer-generated random number. Individuals will then be selected by study investigators in ascending number order. Individuals who are not present on the day will be replaced by the next individual on the list, until the minimum sample size for parasitological testing is achieved.

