## 11. Eligibility Criteria and Justification

Community members must reside within the identified villages, to reduce the contamination of people joining in the study units whom have not received the intervention. Individuals who do not have a signed consent form, are acutely unwell, school-enrolled children, and people who indicate that they have had deworming treatment within previous 12 months, will be excluded from parasitological analyses. Children aged less than one year will be excluded. For ALB only, women in their first trimester of pregnancy will be excluded, as it is not recommended to be taken. Its safety during second and third trimesters of pregnancy has been agreed [38].

PZQ and ALB treatments will be provided in accordance with WHO guidelines [12,39], following discussion and consent; the team will ensure no one is coerced into taking part. For ALB, standard screening questions, including an estimate of gestation period, are included on the participant register. Where there may be doubt about pregnancy, ALB will not be administered. Preschool-aged children will not be treated without a parent/guardian being present. School-enrolled children will receive annual MDA at school, and therefore do not need to be included for treatment or parasitological analysis.

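### The roles of the two comparator sources are not assigned, and nothing in the school selection keeps pupils from the treated communities out of the comparison or identifies them

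*Protocol article*

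**What the plan says.** Three sections of the protocol article describe the comparison with the existing programme.

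- **Section 3 (Study Area and Site Selection)** places all three study communities in Ga South District, in a peri-urban setting around a reservoir. It then states: "Due to the highly focal nature of disease, we will use routine data collected by GHS and CSIR to serve as controls".
- **Section 4 (Study Design)** plans comparisons over time and with school-based MDA in the same districts, at the same time points and in settings of similar prevalence. It adds that "three school-based sites in the same health districts as the study sites will be selected" and that in them "a random sample of school-aged children who currently receive annual MDA will be selected to participate in parasitological examinations and questionnaires". Survey and coverage data held by the national programme "will be analysed for schools in the same health districts that are not included in the surveys".
- **Section 6 (Individual Random Selection)** describes the sampling: "For comparison to annual school-based MDA, a junior school", covering ages 6 to 14, "will be selected at the time the national NTD Control Programme visit occurs". Class lists carry name, age and sex. Pupils are drawn by random number, and absentees are replaced by the next on the list.

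Section 11 (Eligibility) says "School-enrolled children will receive annual MDA at school" and excludes them from the community sample. Its residence rule, meant to limit contamination, applies to community members only. The comparison matters because Section 1 (Background) aims to show a faster decline in infection than annual school-based treatment achieves.

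**The concern.** There are two linked problems.

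First, the only data called controls are routine GHS and CSIR data, yet the comparison described in detail uses newly surveyed pupils. The two differ in sampling, and may differ in diagnostics and timing. An analyst following the article could take either as the basis for the claim of faster decline.

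Second, if the surveyed schools are the comparator, the contrast needs pupils who are under school-based treatment alone. A pupil who lives in a study community shares household and water contact with newly treated adults and preschool children. If expanded treatment lowers transmission, that pupil's infection risk falls too. The Abstract implies this hope when it calls the school-based approach insufficient to control transmission. The comparator then carries part of the intervention effect, and the strategy looks less effective than it is. Aligning ages or survey dates between the samples does not remove this.

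**Working it through.** **1. Which source is the comparator?**

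| Place | Source | Role stated |
|---|---|---|
| Section 3 | Routine GHS and CSIR data | Controls |
| Section 4, comparison (ii) | School-based programme in schools of the same districts | Comparison at the same time points |
| Section 4, last paragraph | Three schools, newly surveyed pupils | Comparison with the national programme |
| Section 4, last paragraph | Programme data from schools outside the surveys | To be analysed; purpose not given |
| Section 6 | Pupils drawn from class lists | Comparison with annual school-based MDA |

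The entries can be reconciled by using both sources. No entry says which source serves which outcome.

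**2. Can sampled pupils live in the study communities?**

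The conditions on the schools are same district, similar prevalence, and selection when the programme visits. None concerns catchment or residence. Section 4 has staff cross-check enrolled children in the treated communities against school MDA, so some children there are expected to be on the school programme. The article does not say where their schools are. Overlap is therefore permitted, but not planned.

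**3. Would it be seen?**

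Name, age and sex do not identify community of residence. The questionnaires may record it, since their full content is not shown, but the article does not provide for using residence in the school comparison.

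**4. Direction of the bias.**

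Let D be the true difference in decline between expanded and school-based treatment, in percentage points. Let c be the share of sampled pupils living in study communities, and d the extra decline those pupils gain indirectly.

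Observed difference = D − c × d

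Since c and d cannot be negative if the indirect effect is a benefit, the observed difference is at most D. If either is zero there is no bias.

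**5. Size, as an illustration only.**

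The article gives no value for c or d and no sample size for the school comparison. Its own figure (Section 15) concerns the before-after change in the communities, and it reproduces:

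7.85 × [0.2 × 0.8 + 0.1 × 0.9] / 0.1² = 196.25; × 1.6 = 314 per site.

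Borrowing 10 points for D and writing d = f × 10, the loss is 10 × c × f points:

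- c = 0.5, f = 0.25: 10 × 0.5 × 0.25 = 1.25 points
- c = 1, f = 0.5: 10 × 1 × 0.5 = 5 points

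For the effect on power, assume 314 independent subjects per group, two-sided 5%, no allowance for clustering, communities at 10% and pupils otherwise at 20%:

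| c × f | Pupils' prevalence | Difference (points) | Power | n per group for 80% |
|---|---|---|---|---|
| 0 | 20% | 10 | 94% | 199 |
| 0.25 | 17.5% | 7.5 | 78% | 330 |
| 0.50 | 15% | 5 | 47% | 686 |
| 0.75 | 12.5% | 2.5 | 17% | 2507 |

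Every input in this table except the 20%, the 10%, the 314 and the 5% level is assumed. Those four are taken from a calculation made for a different contrast.

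**The case against.** The strongest reply is that the overlap is hypothetical. Section 11 says that enrolled children are treated at school but not where. No section says that the communities' own schools will be chosen, the map and design diagram cannot be checked, and school catchments are detail that an article may leave to the full protocol. This stands against any claim that the plan puts its comparator inside the treated communities, which a reader might infer but the text does not support. It does not dispose of the narrower point: the selection conditions and list fields that the article does fix permit overlap and would not reveal it.

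A second reply is that the two sources are complementary. Section 4 itself pairs surveyed schools with programme data from other schools, and the Section 3 sentence may refer to the latter. That is a fair reading, so this is a missing assignment of roles and not an outright contradiction. Nor does Section 3 say that the routine data come from elsewhere.

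Third, Section 6 might be taken to mean a single school. It reads more naturally as naming the type of school used at each site, so little rests on it.

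Fourth, the comparison is not primary. The primary outcome (Section 13), its analysis (Section 14) and the sample size (Section 15) concern change within the communities, and none of the listed secondary outcomes names a school contrast. The bias could not create a false appearance of benefit. All of this stands and limits the weight of the point.

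Finally, the 10-point reduction derives from a cure rate in directly treated children, so it is no guide to indirect benefit in pupils who are already treated every year. That also stands, and it is why the size is left open.

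**Conclusion.** The point holds in a limited form. The article names routine data as controls and describes surveyed pupils as the comparison without giving each source a role. Its stated school conditions do not prevent sampled pupils from living in the study communities, and its class lists would not show it.

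If such pupils are sampled and gain indirectly, the comparison with school-based MDA that Sections 1 and 4 call for is biased toward no difference. The direction rests only on those two conditions, other things being equal. The size cannot be derived from the document, and the figures above show scale under assumed values only.

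A reader might go further and conclude that the trial's main result is compromised. It is not, because the primary before-after analysis does not use the comparator. The point is worth correcting before schools are chosen, since residence that was not recorded is hard to recover later.

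**What to change.** 1. In Section 3, state that the three surveyed schools are the comparator for infection outcomes, and that routine GHS, CSIR and programme data serve as descriptive context and for treatment coverage.
2. Word Section 6 to match Section 4, so that it plainly refers to three schools.
3. Add community of residence to the class list or the pupil questionnaire.
4. Make the school comparison among pupils who do not live in the three study communities. Replace excluded pupils with the next on the same random list, as Section 6 already does for absentees. Any residents who are surveyed are reported separately as a possible spill-over group.
5. Where feasible, prefer schools whose catchment lies outside the study communities. This is a preference and not a requirement: disease is focal, a more distant school may match water exposure less well, and the article does not show that well-matched alternatives exist in the district.

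The cost is a few sentences of protocol text, one extra data field, and a comparison sample that may be somewhat smaller or less closely matched to the local setting. Surveying pupils in schools that already receive MDA does not meet the ethical objection in Section 4 to testing communities where no treatment is offered.
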